## Abstract

**Background:**

Despite many initiatives to enhance the rational use of antibiotics, there remains substantial room for improvement. The overall aim of this study is to optimise the appropriate use of antibiotics in German ambulatory care in patients with acute non-complicated infections (respiratory tract infections, such as bronchitis, sinusitis, tonsillitis and otitis media), community-acquired pneumonia and non-complicated cystitis, in order to counter the advancing antimicrobial resistance development.

**Methods:**

A three-armed cluster randomised trial will be conducted in 14 practice networks in two German federal states (Bavaria and North Rhine-Westphalia) and an added cohort that reflects standard care. The trial is accompanied by a process evaluation.

Each arm will receive a different set of implementation strategies. Arm A receives a standard set, comprising of e-learning on communication with patients and quality circles with data-based feedback for physicians, information campaigns for the public, patient information material and performance-based additional reimbursement. Arm B receives this standard set plus e-learning on communication with patients and quality circles with data-based feedback tailored for non-physician health professionals of the practice team and information material for tablet computers (culture sensitive). Arm C receives the standard set as well as a computerised decision support system and quality circles in local multidisciplinary groups.

The study aims to recruit 193 practices which will provide data on 23,934 patients each year (47,867 patients in total).

The outcome evaluation is based on claims data and refers to established indicators of the European Surveillance of Antimicrobial Consumption Network (ESAC-Net). Primary and secondary outcomes relate to prescribing of antibiotics, which will be analysed in multivariate regression models. The process evaluation is based on interviews with surveys among physicians, non-physician health professionals of the practice team and stakeholders. A patient survey is conducted in one of the study arms. Interview data will be qualitatively analysed using thematic framework analysis. Survey data of physicians, non-physician health professionals of the practice team and patients will use descriptive and exploratory statistics for analysis.

**Discussion:**

The ARena trial will examine the effectiveness of large scale implementation strategies and explore their delivery in routine practice.

**Trial registration:**

ISRCTN, ISRCTN58150046. Registered 24 August 2017.

**Electronic supplementary material:**

The online version of this article (10.1186/s13012-018-0722-0) contains supplementary material, which is available to authorized users.

## Background

Antimicrobial resistance remains high on the health agenda. In Germany, a national policy agenda has reinforced policies to restrain antibiotic prescribing in medicine [1]. Despite decades of scientific research on rational use of antibiotics, and subsequent development of evidence-based practice guidelines [2], there remains a substantial room for improvement. For instance, data on patients with lower respiratory tract infections in German general practice showed that antibiotics were prescribed in 41% of consultations, of which 52% were congruent with guideline recommendations [3]. Strategies to optimise antibiotic prescribing can be effective. A cluster randomised trial in 259 practices in six European countries found that continuing education for physicians reduced their antibiotic prescribing by about 50% (from about 80 to 40%) in patients with respiratory tract infections [4]. However, it is unclear whether these impacts can also be achieved in large scale programs. The focus in the study described here is on scaling up existing implementation strategies to achieve sustainable and large-scale uptake of recommended use of antibiotics in ambulatory care in Germany.

In order to address a wide range of barriers for implementation, the increased rational use of antibiotics requires a complex implementation strategy––an intervention with multiple components interacting with each other. Based on relevant published research, which was identified through a literature review, and experience in quality improvement programs [5, 6], comprehensive implementation programs were developed in close collaboration with participating practice networks as key stakeholders. These programs address physician knowledge and attitudes about the use of antibiotics as well as the ambulatory care team, patient experiences and reimbursement. In the planned study, the effectiveness of these implementation programs will be examined.

A process evaluation will be conducted to understand the mechanisms underlying the effectiveness and to ensure generalizability of intervention effectiveness [7, 8]. Therefore, the process evaluation will explore which components of the programs and which contextual factors contribute to the effects. This knowledge is essential for building an evidence base that informs policy and practice [9]. The process evaluation will focus on the role of networks of ambulatory practices in Germany (‘Arztnetze/Praxisnetze’), in which the ARena project is embedded. These practice networks organise quality improvement and additional reimbursement for specific activities for participating ambulatory practices. Exploring the impact of those networks on antibiotic prescribing is of particular interest. The networks may enhance the contagion of new ideas and practices through various mechanisms of social influence between participating healthcare providers and thus enhance the contagion of knowledge and practices [10]. Reducing antimicrobial resistance is only possible if the large majority of physicians join efforts to reduce antibiotic prescribing. The context of a sustained network may influence physicians’ willingness to cooperate with programs such as ARena because the repeated interaction in the network enhances mutual trust and facilitates the exclusion of non-cooperators [11].

The planned study has three central aims: (a) to determine and compare the effectiveness of three implementation programs to optimise antibiotic prescribing in ambulatory care, (b) to compare the outcomes of the three implementation programs with standard care and (c) to provide insight into the fidelity of the implementation programs, their potential working mechanisms and the impact of health system-related factors on outcomes.

## Methods/design

### Study design

This three-armed (non-blinded) cluster randomised trial consists of different components which aim to achieve sustainable and large-scale uptake of recommended use of antibiotics in ambulatory care in Germany. Each of the three arms will receive a different set of components. The components are based on published research and experiences in improvement programs. Figure 1 presents the study design.

**Fig. 1 Fig1:**
[figure not shown]
ARena study design with three intervention arms and comparison group

The study is planned for 30 months, with an intervention period of 24 months, and split into two parts of evaluation: (a) an *outcome evaluation* based on claims data and (b) a *process evaluation*. The process evaluation will focus on physicians allocated to one of the three intervention arms, non-physician health professionals of the practice team in intervention arm B, as well as stakeholders (see Fig. 2). In Germany, beside physicians, only one non-physician health professional (‘Medizinische Fachangestellte’) is involved in ambulatory care. This role is comparable to medical assistants in the USA [12]. Additionally, a *patient survey* will be conducted in intervention arm B.

**Fig. 2 Fig2:**
[figure not shown]
Process evaluation design of the ARena study

The ARena study is approved by the ethics committee of the Medical Faculty of the University of Heidelberg (reference number S-353/2017).

### Implementation strategies

The implementation strategies will be gradually applied during the intervention period of the study. Intervention group A receives a conventional improvement program with five components targeting physicians and patients. Intervention group B receives the conventional program as well as additional components, which target medical assistants and patients. Intervention group C receives the conventional program and a different set of additional components which target physicians as well as other healthcare providers, like pharmacist and representatives of hospitals or nursing homes. In total, the implementation programs consist of 10 intervention components (Table 1) and take the concept of blended learning into consideration. The specific components are briefly described in this section and characterised in more details according to the TIDieR checklist [13] in Additional file 1.

**Table 1 Tab1:** Overview of intervention components

	Intervention arm		
Intervention components	A	B	C
1) E-learning for physicians	x	x	x
2) Quality circles with data-based feedback for physicians	x	x	x
3) Information campaigns for the public	x	x	x
4) Information campaigns for patients in respective practices	x	x	x
5) Performance-based additional reimbursement (P4P)	x	x	x
6) E-learning for medical assistants		x	
7) Quality circles with data-based feedback for medical assistants		x	
8) Information material available on tablet computers		x	
9) Computerised decision support system (CDSS)			x
10) Quality circles in local multidisciplinary groups			x

Intervention group A (multifaceted intervention program for physicians and patients): E-learning on communication with patients for physicians: Patient-centred communication skills are trained, using videotaped consultations, checklists for use in consultations and patient education material. The focus is on exploration of patient expectations, delayed prescription, if necessary, and shared decision making. Quality circles with data-based feedback for physicians: Four moderated meetings of physicians spread over a period of 2 years, using practice-specific feedback on prescriptions as well as evidence-based information on antimicrobial resistance and prescribing of antibiotics as input. Information campaigns for the public: The information campaign includes social media (Facebook, Twitter, YouTube), explanatory videos, expert interviews, radio and print material. Patient information is provided online (arena-info.org; arena-info.de), using lay language and a user-responsive design. Local healthcare providers are involved, as far as possible. Patient leaflets, which can be individualised to practices, are available in various languages. The information for the public relates to relevant other campaigns on antimicrobial resistance and use of antibiotics, such as the European antibiotics day (18th November––every year). Patient information material: Posters and leaflets are provided to deliver information on antibiotic prescribing to patients with acute non-complicated infections, mainly using existing material from established organisations. Performance-based additional reimbursement: Practices with relatively high numbers of patients with acute respiratory symptoms, bronchitis, tonsillitis, sinusitis or otitis media without antibiotic prescription receive additional reimbursement. The algorithm for the performance-based payment, which will be developed, considers the empirical distribution among practices and the available budget.

Intervention group B (multifaceted intervention program for non-physician health professionals of the practice team and patients):

Components 1–5 plus:6) E-learning on communication with patients for medical assistants: Medical assistants (‘Medizinische Fachangestellte’) receive training, which is focused on communication with patients and practice organisation.7) Quality circles with data-based feedback for medical assistants: Four moderated meetings of medical assistants spread over a period of 2 years, using practice-specific feedback on prescriptions and patient surveys.8) Information material for tablet computers: A tablet computer (culture sensitive tailoring: English, Turkish, Russian, Arabic) is provided to deliver information on antibiotic prescribing to patients with acute non-complicated infections, mainly using existing material from established organisations.

Intervention group C (multifaceted intervention program for physicians with additional strategies):

Components 1–5 plus:9) Computerised decision support system (CDSS): A CDSS is installed in the practice information system. After coding of a relevant diagnosis or antibiotics in the practice system, the CDSS generates a pop-up with a recommendation on prescription of antibiotics based on evidence-based clinical guidelines. The tool is provided by different software providers.10) Quality circles in multidisciplinary groups: Representatives of local healthcare providers (such as ambulatory physicians, hospitals, nursing homes, home nursing, pharmacists) are invited to multidisciplinary, cross-sectoral quality circles. The emphasis of the meetings is on providing information and education on antimicrobial resistance and antibiotic prescribing and to coordinate a regional joint course of action for the rational use of antibiotics.

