#### Financial compensation for study participation

In total, three billing items will be used to reimburse the patient and study-related extra effort. All participating physicians will receive 6€ and medical assistants 5€ per eligible patient and quarter year. Additionally, physicians in intervention group C using the CDSS will receive 2.81€ per eligible patient and quarter year.

Physicians, medical assistants and stakeholders who participate in the interviews within the process evaluation will receive a reimbursement of 50€ each.

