### Primary and secondary outcome measures

The primary as well as the secondary outcomes of the claims data based evaluation are defined and operationalized based on previous research in Germany [17]. Pseudonymized claims data (§§ 295, 300 SGB V) are used to construct different European Surveillance of Antimicrobial Consumption Network (ESAC-Net) indicators [18, 19] measuring the primary and secondary outcomes.

The primary outcome refers to the following index indicator, based on different single ESAC-Net indicators:Percentage of patients with acute non-complicated infections who are treated with antibiotics.

Secondary outcomes refer to the following (ESAC-Net) indicators:2.The use of antibiotics in ambulatory care in defined daily dose (DDD) per 1000 residents (respectively insured persons) per day and region3.Percentage of DDD of broad-spectrum quinolones of all used antibiotics4.Percentage of DDD of broad-spectrum cephalosporins (3rd and 4th generation) of all used antibiotics5.Percentage of patients (18–75 years) with acute bronchitis, patients (> 18 years) with sinusitis, patients (> 2 years) with otitis media and patients (> 1 year) with upper respiratory tract infections/tonsillitis with a prescription of (a) recommended antibiotics, if necessary at all, and (b) less broad-spectrum antibiotics like quinolones6.Percentage of women (> 18 years) with a diagnosis of non-complicated cystitis and a prescription of (a) antibiotics, (b) recommended antibiotics and (c) less broad-spectrum antibiotics like quinolones7.Percentage of patients (18–65 years) with community-acquired pneumonia and a prescription of (a) antibiotics, (b) recommended antibiotics, (c) less broad-spectrum antibiotics like quinolones (> 16 years) and (d) less broad-spectrum antibiotics like cephalosporins or macrolides (> 16 years)8.Percentage of patients with acute non-complicated infections who use medical emergency service9.Percentage of patients with community-acquired pneumonia and hospitalisation

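### The performance payment rewards coded, untreated infections and the primary outcome is a percentage of coded infections, so the pre/post rate can fall through fuller coding alone, and no antibiotic-volume measure is tied to practice or arm to show it

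*Protocol article*

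**What the plan says.** All references are to the protocol article.

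- **Performance payment** (Implementation strategies, component 5, given to arms A, B and C in Table 1): "Practices with relatively high numbers of patients with acute respiratory symptoms, bronchitis, tonsillitis, sinusitis or otitis media without antibiotic prescription receive additional reimbursement". The rule is not final: "The algorithm for the performance-based payment, which will be developed, considers the empirical distribution among practices and the available budget".
- **Per-patient fees** (Financial compensation for study participation): "All participating physicians will receive 6€ and medical assistants 5€ per eligible patient and quarter year". In addition, "physicians in intervention group C using the CDSS will receive 2.81€ per eligible patient and quarter year". None of these fees is linked to whether an antibiotic was given.
- **Source of diagnoses** (Study population): ICD codes recorded by the physician, taken from reimbursement data and grouped by quarter.
- **Primary outcome** (Primary and secondary outcome measures): "Percentage of patients with acute non-complicated infections who are treated with antibiotics".
- **Volume outcome** (same section, secondary outcome 2): DDD "per 1000 residents (respectively insured persons) per day and region".
- **Confirmatory tests** (Data analysis, Outcome evaluation): stage 1 compares before and after within B and within C. Stage 2 does the same within A. The A-B and A-C comparisons follow only if the relevant earlier tests reject. The models contain time, age, gender and random intercepts for patient and practice.
- **Standard-care comparison** (same section): claims of AOK patients in non-participating practices, formed into matched virtual clusters.

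**The concern.** The party that is paid also records the denominator. During the intervention, each additional untreated respiratory or ear infection that is coded may count towards the performance payment, may bring a per-patient fee, and lowers the primary percentage. This needs no bad faith: more complete coding of mild infections that previously went unrecorded is enough.

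That all three arms receive the performance payment does not protect stages 1 and 2. Each arm is compared with its own earlier period, so a shift common to the arms does not cancel. The standard-care practices are outside the scheme, so that comparison is exposed as well. The planned covariates do not correct for a denominator that has itself changed.

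At stake is what a positive result means. Stages 1 and 2 open the hierarchy, and a fall in the percentage would be read as less antibiotic use. The natural check is a volume measure that needs no diagnosis. Secondary outcome 2 is the only one, and as defined it is not tied to practice or arm.

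**Working it through.** **1. The plan's own figures (Sample size calculation).** Inputs: 61% before; 50% after in A; 45% after in B and C; ICC 0.05 for patients in practices and 0.7 for cases in patients; 80 patients per practice and quarter; 80% power.

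- A two-proportion test of 45% against 50% at two-sided 2.5%, with 2:1 allocation, needs 1,423 patients in B (or C) and 2,846 in A before inflation.
- Design effect: (1 + 79 × 0.05) × (1 + 0.7) = 4.95 × 1.7 = 8.415.
- 1,423 × 8.415 ≈ 11,975, against the stated 11,967. For A the result is 23,949, against 23,933. Agreement is within 0.1%, so these inputs are used below.

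**2. Effect of added codes on the primary rate.** Let k be the extra coded patients as a share of the baseline denominator. In the worst case all are untreated and the number treated stays fixed:

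rate = 0.61 / (1 + k); rise in untreated codes = k / 0.39.

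| k (assumed) | Rate | Rise in untreated codes |
|---|---|---|
| 2% | 59.8% | 5% |
| 5% | 58.1% | 13% |
| 10% | 55.5% | 26% |
| 22% | 50.0% | 56% |

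The last row is the whole planned effect in arm A. It equals about 80 × 0.22 ≈ 18 extra untreated codes per practice and quarter. The full B or C effect (61% to 45%) would need k = 0.61/0.45 − 1 = 35.6%, a 91% rise in untreated codes.

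**3. If some added codes belong to treated patients.** With a fraction f of the added codes untreated, rate = (0.61 + (1 − f)k) / (1 + k). At f = 75% and k = 10% this is 0.635/1.10 = 57.7% instead of 55.5%. At f = 39%, the baseline untreated share, the rate stays at 61%. The artefact therefore depends on added codes being untreated more often than at baseline, which is the direction the performance payment rewards.

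**4. Chance that a pre/post test rejects on coding alone.** Assumptions: the stated N divided by 8.415 and split evenly between periods (about 1,422 effective patients per period in A and 711 in B or C), the post period enlarged by k, periods treated as independent, local two-sided level 2.5%, all added codes untreated.

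| k (assumed) | Arm A | Arm B or C |
|---|---|---|
| 2% | 6% | 4% |
| 5% | 26% | 13% |
| 10% | 80% | 47% |
| 22% | >99% | 98% |

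Without enlarging the post period, the 10% row is 78% and 45%. These are illustrations, since the planned mixed model and the true pre/post correlation differ.

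**5. Between-arm contrasts.** Turning 50% into 45% takes 0.50/0.45 − 1 = 11.1% more untreated codes in one arm than in the other. A shift common to both arms does not produce this.

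**6. Which listed outcomes could reveal it.** Outcomes 5 to 9 are conditioned on diagnosis. Outcomes 3 and 4 need no diagnosis but are shares of all antibiotic DDD, so they cannot show a change in total use. Outcome 2 measures volume without a diagnosis, but its stated unit is the region.

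**The case against.** The strongest counter-case is that this is a possibility built on an unfinished payment rule, in an article that announces a separate analysis plan, already plans sensitivity analyses and concedes that claims data have limits. Several parts of it are right.

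- **The payment rule is open.** Whether it will use raw counts or a share is not fixed. It omits cystitis and CAP, and it includes acute respiratory symptoms, which the Study population section does not list among the index diagnoses. Rewarded codes and primary denominator overlap only in part.
- **The 6€, 5€ and 2.81€ fees reward eligible patients, not untreated ones.** They favour more coding but not a direction of treatment.
- **The figures are a worst case.** A 22% rise in the denominator means 56% more untreated codes, and nothing in the document suggests growth of that size.

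Three stronger readings are tempting and are not supported:

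- *That outcome 2 is the only diagnosis-free outcome and cannot be analysed by arm.* Outcomes 3 and 4 are diagnosis-free too. The prescribing physician is recorded, whole networks are allocated, and similar mixed models are planned for secondary outcomes. Analysis by arm is unspecified, not excluded.
- *That differential coding biases A-B and A-C.* Arm C has an additional fee and a decision support tool tied to coding ("After coding of a relevant diagnosis or antibiotics in the practice system, the CDSS generates a pop-up"), but the tool also fires on antibiotics, so its direction is unknown. Medical assistants take part in B, but diagnoses are recorded by physicians. A difference by arm is possible and is not shown.
- *That upcoding will occur.* The document gives no data on it.

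The objection does not remove the exposure of stages 1 and 2. Nor is this only detail left to the analysis plan: the payment target, the coded denominator, the pre/post gate and the regional unit are all stated here, and the problem is their combination.

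**Conclusion.** The point holds as a statement of exposure. Followed as written, the plan could show a lower prescribing rate from fuller coding of untreated infections alone, and no arm-level measure of antibiotic volume is fixed that would show it. The exposure covers the within-arm pre/post tests and the comparison with non-participating practices. It reaches A-B and A-C only under coding shifts that differ by arm.

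Size: with the number treated unchanged and every added code untreated, 5% more coded patients is worth about 3 percentage points, 10% about 5.5 points, and 22% the full 11 points planned for arm A. The coding growth is assumed throughout, and the effect shrinks as more of the added codes belong to treated patients. The primary endpoint and the sample size need not change; this is a worthwhile, low-cost improvement.

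**What to change.** 1. Define secondary outcome 2 by practice or network and by arm, as well as by region.
2. Pre-specify a supportive analysis of the pre/post and standard-care comparisons: patients with at least one antibiotic prescription per 1,000 AOK-insured patients (registered or attending, to be stated) per quarter, in a model like the primary one.
3. Report coded index diagnoses per 1,000 insured patients by arm and period, with the same series for the comparison practices.
4. State that a fall in the primary rate will be interpreted alongside items 1 to 3, without making them a formal gate. A diluted rate is unsuitable as a condition for a confirmatory claim.

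Cost: mainly extra programming. Outcome 2 already needs prescription and insured-person data, and claims are extracted quarterly with the prescribing physician identified. The team should confirm that the extract covers insured patients without an index diagnosis, because the article does not say so explicitly. The drawback is that a rate per insured patient includes antibiotics for other indications, so it is less sensitive and can only be supportive.
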